#### Power Estimation for Stepped Wedge Analysis

Sample size and power were estimated for the stepped-wedge cluster design using simulation under a Hussey-Hughes mixed effects logistic model. With facility totals of 1899—Mbita (n=758), Ogongo (n=294), Ndhiwa (n=598), and Pala (n=249), assuming baseline missed-appointment proportion (p0) of 20% (0.20) and 5 periods, the study has ~80% power to detect an intervention effect (missed visits) corresponding to an odds ratio of 0.75, assuming intracluster correlation coefficient=0.02 (*α*=.05). Sensitivity analyses indicated that power remained ≥70% for odds ratios of 0.80 and intracluster correlation coefficient values up to 0.05 and exceeded 90% for odds ratios of ≤0.70, supporting the robustness of the proposed sample size.

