### Stepped-Wedge Intervention Approach

#### Strategy

A stepped-wedge design was chosen to allow all facilities to receive the intervention, accommodate phased training and app deployment, minimize contamination between sites, and enable within-facility comparisons over time while controlling for secular trends. The 4 CCCs will undergo a standardized readiness assessment, and phased implementation of the intervention will proceed in sequence according to facility readiness, with sites transitioning from standard care to the mHealth intervention arm over an 8-month period. The phased rollout will occur at 2-month intervals across the 4 participating facilities, resulting in 5 study periods (1 baseline and 4 intervention steps) over approximately 8 months. The 2-month interval was selected to align with routine HIV clinic visit schedules in Kenya [18], allow sufficient time for provider training and participant onboarding, and permit stabilization of app engagement before subsequent facility transitions. This interval is consistent with stepped-wedge evaluations of health service and digital interventions [42] and supports the detection of short-term changes in missed clinic visits and adherence behaviors while accounting for secular trends.

We acknowledge that the 2-month step length is relatively short and may limit detection of longer-term intervention effects within each wedge; however, this interval was selected for programmatic feasibility and alignment with routine HIV care cycles, and outcome measures were therefore chosen to capture proximal, short-term indicators of engagement and retention.

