#### Stepped-Wedge Analysis

We will analyze intervention effects using intention-to-treat principles and generalized linear mixed models appropriate to each outcome. Models will include a fixed effect for time period (step) to account for secular trends, a fixed indicator for intervention exposure during each step (within-cluster), and random intercepts for clusters (facilities) to account for within-cluster correlation. Where appropriate, we will include random slopes for time if supported by the data. Covariates prespecified for adjustment include patient-level baseline characteristics (age, gender, income, education, and stigma) and facility-level covariates (facility size and urban or rural). We will use robust SEs (cluster-robust SEs) to ensure valid inference with a limited number of clusters. Additional sensitivity analyses will include per-protocol analyses and models testing for time-by-intervention interaction to explore whether effect sizes change across steps. Primary inference will be 2-sided with *α*=.05. Analyses will be performed in Stata (StataCorp LLC; xtmelogit/xtmixed), and code will be archived with the study repository for reproducibility.

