### Limitations

While this study uses a stepped-wedge cluster randomized design, several limitations should be noted. First, the number of clusters (health facilities) is small, which may limit statistical power and the ability to control for facility-level confounding. The small number of clusters limits the precision with which facility-level confounders can be modeled and reduces degrees of freedom for estimating random effects. As a result, adjustment for cluster-level confounding is restricted to a limited set of prespecified facility characteristics (eg, size and urban-rural setting), and residual confounding at the facility level cannot be entirely ruled out. To mitigate this limitation, analyses will include fixed effects for time, intention-to-treat estimation, and triangulation with qualitative data to support interpretation of observed effects. Second, reliance on self-reported survey measures for some implementation outcomes (eg, acceptability and adherence) and masculinity factors may introduce recall or social desirability bias. Third, inclusion criteria requiring smartphone or tablet ownership may exclude more men from resource-limited countries, potentially limiting the generalizability of findings. Finally, variations in how the intervention is implemented across facilities—due to staffing, infrastructure, or engagement differences—may influence observed effects. Despite these limitations, the study’s mixed methods approach and triangulation of data sources will enhance the robustness and contextual relevance of the findings.

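### The ~80% stepped-wedge power assumes no facility-by-period variation, and the robustness claim never tests that assumption; the planned standard errors do not protect against it with 4 facilities

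*Protocol article*

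**What the plan says.** The section Power Estimation for Stepped Wedge Analysis says: "Sample size and power were estimated for the stepped-wedge cluster design using simulation under a Hussey-Hughes mixed effects logistic model". Its inputs are the four facility totals (758, 294, 598 and 249; 1899 men), "assuming baseline missed-appointment proportion (p0) of 20% (0.20) and 5 periods", ICC 0.02 and α .05. It reports about 80% power at an odds ratio (OR) of 0.75. The sensitivity statement gives at least 70% power for OR 0.80 and ICC up to 0.05, and more than 90% for OR 0.70 or lower. It concludes that this is "supporting the robustness of the proposed sample size".

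The Stepped-Wedge Analysis section plans period fixed effects, an exposure indicator and "random intercepts for clusters (facilities) to account for within-cluster correlation". Random slopes for time are optional. Cluster-robust standard errors are meant to keep inference valid with few clusters. The Strategy section describes the layout as "resulting in 5 study periods (1 baseline and 4 intervention steps) over approximately 8 months". The Limitations section accepts that implementation may vary across facilities through "staffing, infrastructure, or engagement differences".

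**The concern.** A Hussey-Hughes model with one facility intercept assumes that two men at the same clinic are as correlated 8 months apart as within one 2-month period, that is, a cluster autocorrelation (CAC) of 1. If a clinic's missed-visit rate moves between periods for local reasons, that movement adds error to the treatment comparison which more men per clinic cannot average out.

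The comparison is largely within facility, so a constant facility effect nearly cancels and the ICC has little influence. Varying the ICC therefore says little about robustness. Varying the OR changes the effect to be detected and does not test the variance assumption.

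Two things are at stake: the stated power for the primary outcome, and the type I error of an analysis that leaves this variation out.

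**Working it through.** **Inputs.** From the article: facility sizes, 5 periods with one facility crossing per step, p0 = 0.20, OR 0.75, ICC 0.02, two-sided 5%. The order is not fixed ("phased implementation of the intervention will proceed in sequence according to facility readiness"), so results are averaged over all 24 orders. Assumed: every man contributes one observation per period. If 1899 were instead the total over all periods, power would be only about 27%, so the per-period reading is the one that matches the article. Also assumed, because the documents give neither: the CAC and the within-person correlation r.

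**Formula.** For facility i with n men, the covariance of its five period values is

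V_i = σ_b²[CAC·J + (1−CAC)·I] + D[(1−r)I + rJ]D.

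On the logit scale, σ_b² = ICC/(1−ICC) × π²/3 = 0.0671 and D holds √(1/(n·p(1−p))). On the proportion scale, with s² = p̄(1−p̄), σ_b² = ICC·s² and D holds √(s²(1−ICC)/n); p̄ is the mean of 0.20 and 0.158. SE² is the treatment element of (Σ X_i′V_i⁻¹X_i)⁻¹, and power = Φ(|effect|/SE − 1.96).

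**Step 1: the stated figure.** On the logit scale with CAC 1 and r = 0, SE is 0.1002. Then |ln 0.75|/0.1002 = 0.2877/0.1002 = 2.87, and Φ(0.91) = 82% (79.5 to 84.2% across orders). The ~80% reproduces.

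**Step 2: the ICC.** Power at ICC 0.01, 0.02, 0.05 and 0.10 is 82.9, 81.9, 81.3 and 81.0% (logit scale). From 0.02 to 0.05 it moves 0.6 points.

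**Step 3: facility-period drift, OR 0.75, ICC 0.02.**

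| CAC | Logit, r = 0 | Proportion, r = 0 | Logit, r = 0.2 | Proportion, r = 0.2 |
|---|---|---|---|---|
| 1.00 | 82% | 82% | 89% | 90% |
| 0.98 | 78% | 75% | 86% | 82% |
| 0.95 | 73% | 66% | 80% | 72% |
| 0.90 | 66% | 54% | 72% | 59% |
| 0.80 | 56% | 40% | 60% | 43% |

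Using 0.16 for s² lowers the proportion-scale columns by about 3 to 4 points.

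The drift involved is small. On the proportion scale its SD is √(0.02 × 0.16 × (1−CAC)), or 0.8, 1.3, 1.8 and 2.5 percentage points for CAC 0.98 to 0.80. On the logit scale it is about 0.6 to 1.9 points. For comparison, binomial noise per facility-period is √(0.16/758) = 1.5 points at the largest clinic and √(0.16/249) = 2.5 at the smallest.

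**Step 4: the OR 0.80 figure, no drift.** With SE 0.0991, 0.2231/0.0991 = 2.25 and Φ(0.29) = 61%; the range is 58 to 64% over orders and ICC 0.02 to 0.05. The article's own numbers show the same. Power of 80% at OR 0.75 implies SE = 0.2877/(1.96 + 0.842) = 0.1027. At OR 0.80 that gives Φ(0.2231/0.1027 − 1.96) = Φ(0.21) = 58%. At OR 0.70 it gives Φ(0.3567/0.1027 − 1.96) = 93%, which agrees with the article's figure of more than 90%.

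**Step 5: type I error.** Null data were simulated 4000 times per setting and fitted with a logistic model with facility and period effects, a close stand-in for the random-intercept model. The sandwich variance carries a 4/3 correction.

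| Logit drift SD | Model-based z | Cluster-robust z | Cluster-robust t(3) | Overdispersion-scaled t(11) |
|---|---|---|---|---|
| 0 | 5% | 23% | 9% | 2% |
| 0.05 | 8% | 23% | 10% | 3% |
| 0.10 | 15% | 25% | 10% | 5% |
| 0.15 | 25% | 26% | 11% | 6% |

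The 11 df are 20 cells minus 4 facility, 4 period and 1 treatment parameter.

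**The case against.** **The sensitivity analysis also varied the OR.** This is correct, so a reader should not infer that only the ICC was varied. The accurate statement is that the ICC is the only correlation parameter varied.

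**80% is not a best case.** A reader might infer that it is, but the same men are followed, and positive within-person correlation raises power: at r = 0.2 with no drift it is about 89%. The documents give neither r nor the CAC, so no single corrected power can be stated, and 40 to 75% is not an established figure. What stands is that the lower end stays well below 80% even at r = 0.2.

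**The documents do not report drift.** The Limitations section speaks of differences across facilities in how the intervention is implemented, not of period-to-period movement in missed visits. That step is an inference. The same section already concedes that few clusters may limit power, and random slopes for time are allowed; but a linear slope does not absorb irregular period-to-period shifts.

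**Model-based standard errors are not what is planned.** Also correct: the 8 to 25% under drift describes an analysis without the planned robust errors. The planned errors do not repair it, however. With 4 clusters they are too liberal even when there is no drift (Step 5).

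**Conclusion.** The point holds in limited form. The ~80% is right under its own model but conditional on there being no facility-by-period variation, and the claim of robustness is unsupported because that condition was never varied. Over the assumed CAC range of 0.98 to 0.80, power at OR 0.75 is about 78 to 56% (logit scale) or 75 to 40% (proportion scale), rising to about 86 to 60% or 82 to 43% at r = 0.2. These ranges rest on assumed correlations and on an analysis that allows for drift; an analysis that ignores drift pays in false positives instead.

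Two parts need no assumed correlation. Power of at least 70% at OR 0.80 is inconsistent with about 80% at OR 0.75. And cluster-robust errors on 4 facilities do not hold the 5% level: about 23% with a normal reference and 9% with t(3), without any drift.

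**What to change.** **Stepped-Wedge Analysis section.** Replace the cluster-robust standard errors with primary inference on the 20 facility-period cells: facility and period effects, a variance scaled for overdispersion (scale not below 1), and a t reference on about 11 df. Simulated type I error is 2 to 6%. A model with facility and facility-by-period random intercepts is an alternative if paired with an equivalent small-sample method; its type I error was not simulated here and should be checked for 4 facilities first.

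**Power section.** State that ~80% is conditional on no facility-by-period variation. Report power over a stated range of CAC and within-person correlation, using the chosen test. Correct the OR 0.80 figure. Delete the clause "supporting the robustness of the proposed sample size".

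**Cost.** A change of test and a rerun of the power simulation, with no more men or facilities. The stated power will be less favourable and the confidence interval wider. If there is no drift, the proposed test has about 67 to 71% power at OR 0.75 instead of about 81%, a loss of 10 to 14 points. The article expects follow-up to finish in August 2026, so the change can be fixed before outcomes are analysed.

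### Stated power of at least 70% at an odds ratio of 0.80 does not fit with about 80% at 0.75; the stated inputs give about 60%

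*Protocol article*

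**What the plan says.** Under Power Estimation for Stepped Wedge Analysis, the protocol article says that power was obtained "using simulation under a Hussey-Hughes mixed effects logistic model", with facility sizes of 758, 294, 598 and 249 men (1899 in all) and "assuming baseline missed-appointment proportion (p0) of 20% (0.20) and 5 periods". The headline is that "the study has ~80% power to detect an intervention effect (missed visits) corresponding to an odds ratio of 0.75", at an intracluster correlation (ICC) of 0.02 and alpha of .05.

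Two sensitivity statements follow. The first is "Sensitivity analyses indicated that power remained ≥70% for odds ratios of 0.80 and intracluster correlation coefficient values up to 0.05". The second is that power was above 90% at odds ratios of 0.70 or lower. The closing clause treats these figures as evidence that the sample size is robust.

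The Stepped-Wedge Analysis section makes the primary inference two-sided at .05 and names cluster-robust standard errors. The Limitations section concedes that "the number of clusters (health facilities) is small, which may limit statistical power".

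**The concern.** The three power figures describe one design: the same facilities, periods, baseline proportion and alpha. Between odds ratios of 0.75 and 0.80 only the effect changes, and the standard error barely moves. The drop in power is then nearly fixed once the 80% is given, and a fall to only 70% looks too small.

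Missed appointments is the primary clinical outcome, and this paragraph is its only power justification in the article. If power at 0.80 is about 60%, the chance of missing a true effect of that size is about 40%, not at most 30%. A reader relying on the robustness statement would give a null result more weight against a modest benefit than the design can bear.

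**Working it through.** **Inputs.** From the power section: facility sizes 758, 294, 598, 249; 5 periods; p0 = 0.20; ICC 0.02, with 0.05 as the sensitivity value; alpha .05. From the Strategy section: one baseline period and four steps, with facilities entering in order of readiness, so all 24 orders were examined. From the Stepped-Wedge Analysis section: two-sided testing. Assumption (the article gives no per-period count): every man contributes one outcome in every period.

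**Step 1: scaling from the article's own headline.** With a roughly constant standard error, the expected test statistic is proportional to |ln OR|.

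- 80% power at OR 0.75 means an expected statistic of 1.960 + 0.842 = 2.802.
- ln(0.80)/ln(0.75) = 0.2231/0.2877 = 0.776.
- At OR 0.80: 2.802 × 0.776 = 2.173, and Φ(2.173 − 1.960) = Φ(0.213) = **58%**.
- At OR 0.70: ln(0.70)/ln(0.75) = 1.240; 2.802 × 1.240 = 3.473, and Φ(1.513) = 93%. This agrees with the text.
- In reverse, 70% at OR 0.80 needs 1.960 + 0.524 = 2.484; 2.484/0.776 = 3.203, and Φ(3.203 − 1.960) = **89%** at OR 0.75.

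Scaling on the risk difference gives 60% at OR 0.80. Using a t reference with 3 to 15 degrees of freedom, calibrated to 80% at OR 0.75, gives 58% to 61%.

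**Step 2: direct calculation.** The model is logit(p) = period effect + β × exposure + facility effect.

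- Facility variance: τ² = [ICC/(1 − ICC)] × π²/3.
- Variance of each facility-period log odds given the facility effect: 1/[n p(1 − p)]. Here p = 0.20 in control periods and p = 0.25·OR/(1 + 0.25·OR) under exposure, which is 0.167, 0.158 and 0.149 for OR 0.80, 0.75 and 0.70.
- The standard error of β comes from generalised least squares over the 20 facility-periods, and power = Φ(|ln OR|/SE − 1.960).

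At ICC 0.02, with the SE averaged over rollout orders:

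- OR 0.75: 0.2877/0.1002 = 2.87; Φ(0.91) = 82%
- OR 0.70: 0.3567/0.1014 = 3.52; Φ(1.56) = 94%
- OR 0.80: 0.2231/0.0991 = 2.25; Φ(0.29) = 61%

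| OR | Article | ICC 0.02, mean (range over orders) | ICC 0.05, mean (range over orders) |
|---|---|---|---|
| 0.75 | ~80% | 81.9% (79.5–84.2) | 81.3% (78.8–83.6) |
| 0.70 | >90% | 94.0% (92.6–95.3) | 93.7% (92.2–95.0) |
| 0.80 | ≥70% | **61.5% (58.8–64.1)** | **60.8% (58.1–63.4)** |

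**Step 3: simulation check.** Logistic data were generated with random facility intercepts and random rollout order (2000 runs per cell), fitted with facility and period effects, and tested with a model-based Wald test. At ICC 0.02, power was 81.5% at OR 0.75, 93.4% at 0.70 and 60.3% at 0.80. At ICC 0.05, power at 0.80 was 60.1%. The Monte Carlo error of the last figure is √(0.6 × 0.4/2000) = 1.1 points, against a gap of about 10 points.

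**Step 4: other readings.**

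- *A different ICC.* Power at 0.80 passes 70% only with an ICC near zero. At 0.0001 it averages 80%, but power at 0.75 is then 94%, not about 80%.
- *Two separate scenarios* (OR 0.80 at ICC 0.02; ICC 0.05 at OR 0.75). The second holds; the first still gives about 61%.
- *One-sided alpha throughout.* (1.645 + 0.842) × 0.776 = 1.929; Φ(1.929 − 1.645) = 61%. About 70% appears only if OR 0.80 is tested one-sided and OR 0.75 two-sided.
- *1899 outcomes spread over the five periods.* Power at 0.75 is then only about 24% to 27%, so this cannot be the basis of the headline.

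**The case against.** The strongest reply is that the scaling presumes a near-normal statistic with a correctly sized test, whereas the analysis section names cluster-robust standard errors and the power section does not say which standard error its simulation used. With four clusters, a facility-clustered sandwich statistic referred to the normal distribution has heavy tails, and its power curve is flatter. Simulated that way, with 65% of men observed per period and no correction, power is about 82% at OR 0.75, 70% at 0.80 and 91% at 0.70. With 85% observed and a K/(K − 1) correction it is about 84%, 70% and 93%. Both come close to the published pattern.

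Part of this stands: the stated trio is not impossible for every conceivable test. It does not rescue the sentence. The observed fractions are chosen to fit and appear nowhere in the article. The same tests reject a true null in roughly 21% to 28% of runs, so they do not deliver power at the stated alpha of .05. If that is how the figures arose, the remedy is still to restate them.

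It is also fair to say that the disputed figure is a sensitivity clause, that it changes no endpoint or analysis, and that the Limitations section already warns of limited power. That general warning does not correct a specific number.

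**Conclusion.** The point holds for the OR 0.80 clause. At a true two-sided 5% level, and with all 1899 men observed in each period, power there is about 60% (58% to 64% across ICC 0.02 to 0.05 and all rollout orders). That is 6 to 12 points below the stated minimum. The mismatch with the headline needs only a roughly constant standard error and a correctly sized test; the direct figures also need the full-observation assumption.

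Three stronger readings should be resisted.

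- A reader might infer that the whole power paragraph is wrong. It is not: about 80% at 0.75, above 90% at 0.70, and the insensitivity to ICC at 0.75 all reproduce.
- A reader might want to substitute the power of a particular small-sample test. The article names no such test, so no such figure can be presented as the power of the planned analysis.
- A reader might infer much lower power from facility-by-period variation or from men without an appointment in a given period. The article gives no values for either, so such figures would be illustrations under added assumptions. They are not needed to show the inconsistency.

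**What to change.** In Power Estimation for Stepped Wedge Analysis:

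1. Rerun the simulation and restate power at OR 0.80 as about 60% for ICC 0.02 to 0.05. If the inputs behind the OR 0.75 figure were misreported, correct that figure and its inputs instead.
2. State how many men contribute an outcome in each period.
3. State the standard error and reference distribution used in the simulation, and report the simulated type I error alongside power. This matters with four clusters and cluster-robust standard errors.
4. Remove the closing robustness claim, or limit it to the effects for which it holds, making clear that it does not extend to OR 0.80.
5. Label any scenario for attendance or facility-by-period variation as an assumption.

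The cost is a rerun, revised wording and a less favourable stated power. No extra participants are required; the 1899 are already all the men aged 18 to 55 in HIV care that the four facilities are said to serve.

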### Pre- and Postassessment of Implementation Outcomes

#### Participants and Recruitment

The primary study population will comprise men who initiated HIV care and treatment in 2016 or later, following the updated national HIV treatment guidelines. Eligible participants must be between 18 and 55 years of age, own a smartphone or tablet, and be able and willing to provide written informed consent (Multimedia Appendix 1). Men with severe comorbidities or chronic coinfections (eg, cancer or hypertension) that may affect the adoption or use of mHealth interventions will be excluded. Only men who are primarily enrolled at 1 of the 4 participating facilities during the study period will be included. Participant recruitment in each CCC will proceed according to probability proportional to size sampling until the required sample size of 347 participants is reached. Recruitment will occur during routine clinic visits in each facility before the stepped-wedge rollout of Nishauri. Trained study staff or peer educators will introduce the study to clients, provide study information, and collect contact information from those expressing interest. Screening for eligibility will take place in private, either in a clinic or at a location convenient and confidential for the participant. Those who are eligible and interested will then undergo written informed consent.

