## Introduction

Globally, men are 27% less likely than women to seek HIV testing and often present to care at later stages of illness [1]. In sub-Saharan Africa, men’s participation in HIV care is further constrained by cultural expectations that prioritize economic provision, requiring men to focus on work and income generation over health-seeking. Additionally, norms around emotional suppression discourage men from expressing vulnerability or seeking support, including attending health services [2,3]. Recent studies highlight that men who conform to traditional masculine norms are less likely to attend routine HIV care and more likely to disengage from treatment [4-6]. Despite advances in antiretroviral therapy (ART) and HIV care services, men experience persistent barriers to accessing and engaging with care. Masculine norms around strength, stoicism, and self-reliance often discourage men from seeking health services, including HIV testing and treatment [4], contributing to lower engagement and adherence [7,8]. The lack of men-targeted interventions compounds these challenges, making it critical to develop and evaluate strategies that effectively engage men in care to achieve the Joint United Nations Programme on HIV/AIDS 95-95-95 targets by 2030.

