### Study Setting

We will conduct this study in 4 subcounty HIV Comprehensive Care Clinics (CCC) in Homa Bay County, Kenya—Mbita, Ogongo, Ndhiwa, and Pala. Homa Bay County was chosen for its highest HIV prevalence, 16.2% [18] in Kenya, making it suitable to assess the implementation process and outcomes of an mHealth intervention for enhancing HIV care. The county covers an area of about 3154 km^2^ [38,39]. As of the 2019 Kenya National Census, it had an estimated population of approximately 1.1 million people [39]. There are approximately 160 health facilities providing HIV comprehensive care services across the county. ART uptake is at 96%, while viral load suppression (VLS) prevalence is at 83.8% among people living with HIV, with significant disparities between men and women [18,27,40].

The 4 health facilities have been selected based on feasibility factors such as patient volume and mobile network coverage, representativeness of diverse service delivery contexts, and requirements of the stepped-wedge design to ensure adequate clusters while minimizing contamination. They serve a total of 1899 men living with HIV aged 18‐55 years: Mbita (n=758), Ogongo (n=294), Ndhiwa (n=598), and Pala (n=249). The average distance between each neighboring facility is 25 km. Mbita and Ndhiwa subcounty hospitals are situated in an urban setup, while Ogongo and Pala subcounty health centers are located in relatively rural setups.

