#### Power Calculation for the Pre- and Postassessment

With 347 participants, an anticipated 10% attrition rate (effective n≈312), and a primary binary uptake outcome, the study will have adequate power to examine associations between key predictors (health literacy, technology acceptance, and masculinity) and adoption of Nishauri. Assuming an uptake rate of ~70% (adopters: n≈243; nonadopters: n≈104) as seen in other studies [22,23], we will have >80% power (*α*=.05) to detect moderate associations corresponding to odds ratios of roughly 1.7‐2.0 or higher, depending on predictor prevalence. Sensitivity analyses showed that with effective sample sizes ranging from 280 to 330 participants, the study would retain ≥80% power to detect odds ratios between 1.7 and 2.0, depending on predictor prevalence.

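### The survey cohort is labelled a probability-proportional-to-size sample, but within each clinic it consists of volunteers met at routine visits, so men who often miss visits are under-represented

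*Protocol article*

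**What the plan says.** The Participants and Recruitment section of the protocol article names the sampling method for the survey cohort: "Participant recruitment in each CCC will proceed according to probability proportional to size sampling until the required sample size of 347 participants is reached". It then describes how men are reached: "Recruitment will occur during routine clinic visits in each facility before the stepped-wedge rollout of Nishauri". On selection within a clinic it says: "Trained study staff or peer educators will introduce the study to clients, provide study information, and collect contact information from those expressing interest". It describes no list from which men are drawn, no random selection within a facility, and no route to men who are not attending.

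Study Setting gives the four facilities and their numbers of men aged 18 to 55 (758, 294, 598 and 249, total 1899). All four are in the study. The Introduction states that "men who conform to traditional masculine norms are less likely to attend routine HIV care and more likely to disengage from treatment". The second objective concerns masculine identity and uptake, and the power calculation for the pre- and postassessment names masculinity as a predictor of adoption.

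The Limitations section lists few clusters, self-report, the smartphone or tablet requirement and variable implementation. It does not mention that survey participants are recruited only from attenders.

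**The concern.** Probability-proportional-to-size selection gives each unit a known chance of entry. When every facility is included, no facility is selected, and the method reduces to site quotas in proportion to size. The chance that a given man enters then depends on whether he comes to the clinic while staff are recruiting and whether he volunteers. Neither probability is known.

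This matters more here than in most surveys because attendance is close to what the study is about. By the article's own account, men with stronger traditional norms attend less. Recruiting through attendance therefore filters the cohort on engagement and on a correlate of a main predictor. The adoption level, the acceptability scores and the predictor associations all come from that filtered group. Under the present label, a reader would take them to describe the eligible men at these clinics.

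**Working it through.** **Plan's own figures.** The article plans on "With 347 participants, an anticipated 10% attrition rate (effective n≈312), and a primary binary uptake outcome": 347 × 0.90 = 312.3, which agrees. The facility counts sum correctly: 758 + 294 + 598 + 249 = 1899.

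**What size-proportional sampling can do here.** If the facility counts in Study Setting are the size measure (the article does not say), the quotas are 347 × N / 1899:

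- Mbita: 347 × 758 / 1899 = 138.5, about 139
- Ogongo: 347 × 294 / 1899 = 53.7, about 54
- Ndhiwa: 347 × 598 / 1899 = 109.3, about 109
- Pala: 347 × 249 / 1899 = 45.5, about 45

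This fixes the site shares and says nothing about which men are taken within a site.

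**Illustration of the selection.** The stepped-wedge power section supplies the mean missed rate: "assuming baseline missed-appointment proportion (p0) of 20% (0.20) and 5 periods". How missed visits are spread between men is not given, so it is assumed:

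- 20% of men miss 60% of visits and 80% miss 10%.
- Mean: 0.20 × 0.60 + 0.80 × 0.10 = 0.20, matching the plan.
- A man with missed rate m and k scheduled visits in the window can be met with probability 1 − m^k. Misses are taken as independent, and willingness to volunteer as equal in both groups.

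The number of visits k is also an assumption. The Abstract puts recruitment in September to November 2025, and the stepped-wedge Strategy section aligns its 2-month interval with routine visit schedules. One or two scheduled visits per man is therefore reasonable.

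*One visit:*
- Frequent missers met: 0.20 × 0.40 = 0.08. Others met: 0.80 × 0.90 = 0.72.
- Share of recruits: 0.08 / 0.80 = 10%, against 20%.
- Cohort missed rate: 0.10 × 0.60 + 0.90 × 0.10 = 15%, against 20%.

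*Two visits:*
- Frequent missers met: 0.20 × (1 − 0.36) = 0.128. Others met: 0.80 × (1 − 0.01) = 0.792.
- Share of recruits: 0.128 / 0.920 = 13.9%.
- Cohort missed rate: 0.139 × 0.60 + 0.861 × 0.10 = 17.0%.

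**Other assumed mixtures with the same 20% mean:**

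| Mixture | Frequent missers in clinics | Among recruits, k = 1 | Among recruits, k = 2 | Cohort missed rate, k = 1 / k = 2 |
|---|---|---|---|---|
| 25% miss 50%, 75% miss 10% | 25% | 15.6% | 20.2% | 16.3% / 18.1% |
| 10% miss 65%, 90% miss 15% | 10% | 4.4% | 6.2% | 17.2% / 18.1% |
| 20% miss 80%, 80% miss 5% | 20% | 5.0% | 8.3% | 8.8% / 11.2% |

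Under these assumptions the direction is the same whenever men differ in how often they miss visits. The cohort missed rate ranges from 8.8% to 18.1%, against 20%.

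**The case against.** The best defence is that, with all four sites included, the wording is loose language for proportional site allocation. The article also nowhere announces design-based population estimates, and its Discussion concedes that findings may be specific to the county. The allocation reading is fair for the site quotas. It does not rescue the label, which is attached to recruitment within each clinic, where the next sentences describe volunteers among attenders.

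Several stronger readings might be inferred, and the document does not support them:

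- *A man who misses a visit during recruitment is shut out.* He can be met at another visit in a window of about three months. Only men who attend nothing in that window have no chance of entry.
- *The trial's primary clinical outcome is distorted.* The Outcomes section takes missed appointments from facility records, and the stepped-wedge part applies no individual exclusions. Survey recruitment does not touch it, and the missed rates worked out here only gauge how selective the cohort is.
- *The masculinity-adoption association is biased in a known direction.* A narrower range of a predictor does not by itself bias a regression association. Bias requires selection that is also related to adoption, or an effect that differs by attendance. Neither is shown.
- *The quotas are wrong because 1899 includes men ineligible for the survey.* The article does not state the size measure for the survey, so this rests on inference.

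**Conclusion.** The point holds for the survey cohort. The stated sampling property does not exist within sites, frequent missers are under-represented, and the Limitations section does not say so. In the main illustration they are 10% to 14% of recruits instead of 20%, with a cohort missed rate of 15% to 17% instead of 20%. These sizes rest on an assumed spread of missed visits, one or two scheduled visits in the window, independent misses and equal willingness to volunteer. The true size could be smaller or larger.

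What is at stake is how the adoption level, acceptability and predictor associations may be described and generalized. No effect on adoption itself has been quantified, and the direction of any bias in the masculinity-adoption association is unknown. This should be corrected, but it does not threaten the stepped-wedge inference.

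**What to change.** 1. Replace the sampling label with: clinic attenders who volunteered, with site quotas proportional to facility size.
2. Compare recruits with men on each facility's register aged 18 to 55 who started care in 2016 or later, by facility, age and missed appointments before rollout. The facility records that the Outcomes section already plans to retrieve can serve for this.
3. Report adoption and the masculinity-adoption models weighted to that group as a sensitivity analysis, beside the unweighted results.
4. Add attender-only recruitment to the Limitations section.

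The cost is a change of wording and one additional analysis. The weighted results will lose some precision. Weights cannot represent men who had no chance of selection, and cannot adjust for device ownership if the register does not record it.

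Two further steps are not recommended. Making weights to the full register of men aged 18 to 55 the primary analysis would target men whom the survey's eligibility criteria exclude. Late recruitment from missed-appointment lists would be a new route needing ethics approval. The Abstract reports recruitment as concluded, and the Results section reports baseline collection complete in three facilities, so a new route at a remaining site would mix recruitment mode with facility. The phone contacts under Retention Strategy serve men already enrolled, and the community outreach in the stepped-wedge Strategy section serves app training, so neither is an existing recruitment route.
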